### 7.4 Screening and Baseline Assessment

After ICF has been obtained at the first pre-randomization visit, the consented participant will undergo initial screening which will include basic medical and

medication history, and hip BMD measurement.

At the end of the first pre-randomization visit, the consented participant will be scheduled for a second visit within about 1 week for screening. The participant will be asked to do transvaginal ultrasound and blood test to check endometrial thickness, and kidney and liver function, etc. A venous blood sample (approx. 10 ml) will be taken for blood biochemistries and a urine sample to determine if the individual meets eligibility criteria. A screening log will be recorded by each site to each candidate.

The assessment will be included:

- Medical and medication history(including history of falls);
- Physical examination (including height and weight);
- 12-lead ECG;
- Vital signs: blood pressure, temperature, pulse and heart rate;
- DXA scan of proximal femur;
- Samples: blood count, liver and kidney function, 25 (OH) vitamin D, osteocalcin, 17 $\beta$ -estradiol and urine deoxypyridinoline;
- Safety.

At the third visit, those participants who meet the eligibility criteria will be enrolled in the trial and continue with a further baseline assessment and randomization.

All participants who enter into the screening period will receive a unique subject identification number. Participants numbers will be assigned in sequential order. The subject identification number must remain constant throughout the clinical trial, that's to say, it must not be changed at the time of re-screening, enrollment, or randomization. This number will not be the same as the randomization number assigned for the study. All the participants must be subjected to physical examination, efficacy and safety assessment during the recruitment.

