#### With:

A fall is defined as any event that led to an unplanned, unexpected contact with a supporting surface. Falls resulting from pathologic fracture, major trauma or facial trauma, and/or unavoidable hazards such as transient ischemic attacks, chair collapsing or cerebrovascular accidents will be excluded. A faller is defined as the participants sustained at least one fall or more. Information about new falls while on study will be documented using form, included the date of fall and related-injury. The number of falls is accumulated. **The cumulative incidence of fallers will be calculated as the total number of participants with first fall at each time point divided by the number of participants at risk.** A copy of radiograph confirming the fracture will be obtained.

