**All the analyses will use randomly assigned patients under ITT principle. For**

patients missing data after the baseline, the LOCF approach use to analyze the longitudinal data.

The numbers of falls and adverse events will perform by chi-square test. Kaplan–Meier analysis will be calculated in order to demonstrate differences in number of fallers over time. The time to first fall will be analyzed using a Cox regression analysis providing a 95% confidence interval.

Repeated-measures ANOVA analysis should be carried out between two groups and four times (baseline, 12, 24 and 36 months). Within-subjects results will be used *t*-test on the percentage change from the baseline value. All tests will be used two-sided and set at the 5% level.

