| Endpoints                  | 
Endpoints are to be evaluated for BSYJF versus placebo.
 
Primary endpoint:
 
 
1. Number of falls at month 36.
 
 
Secondary endpoints:
 
 
1. Change from month baseline at month 36 in femoral neck BMD;
 
2. Change from month baseline at month 36 in lean mass of left thigh;
 
3. Change from month baseline at month 36 in TUG test;
 
4. Change from month baseline at month 36 in biomarkers of bone turnover (osteocalcin and deoxypyridinoline).
 
5. Change from month baseline at month 36 in endometrial thickness;
 
6. Change from month baseline at month 36 in estradiol;
 
7. Nature, frequency and severity of adverse events and their relationship to treatment.
 
 
Additional endpoint:
 
8. Number of falls at the end of 10 years extension follow-up.
 |
| Statistical considerations | 
All the analyses will use all randomly assigned patients under ITT principle. For patients missing data after the baseline, the LOCF approach use to analyze the longitudinal data. The number of falls at month 36 and adverse events will perform by chi-square test. Kaplan–Meier analysis will be calculated in order to demonstrate differences in number of fallers over time. The time to first fall will be analyzed using a Cox regression
                                                                                                                                                                                                                                                                                                                                                                                                                                                                                                                 |

|  |                                                                                                                                                                                                                                                                                                                                                                                                                                                                                                    |

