|--|----------------------------------------------------------------------------------------------------------------------------------------------------------------------------------------------------------------------------------------------------------------------------------------------------------------------------------------------------------------------------------------------------------------------------------------------------------------------------------------------------|
|  | 
analysis providing a 95% confidence interval. Repeated-measures ANOVA analysis should be carried out between two groups and four times (baseline, 12, 24 and 36 months). Within-subjects results will be used t-test on the mean percentage change from the baseline value. All tests will be used two-sided and set at the 5% level.
 
Additional analysis:
Number of falls at the end of 10 years extension follow-up will be performed by chi-square test.
 |
|--|----------------------------------------------------------------------------------------------------------------------------------------------------------------------------------------------------------------------------------------------------------------------------------------------------------------------------------------------------------------------------------------------------------------------------------------------------------------------------------------------------|

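### The sole primary endpoint is an accumulated count of falls, but its chi-square test does not define whether falls or women are tabulated and uses no follow-up time

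*Supplement*

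**What the plan says.** Amendment 1 reduced four primary endpoints to one, and Amendment 2 kept it. The current synopsis lists it as "Number of falls at month 36". Section 12.3, as replaced by Amendment 1, makes it a running count: "The number of falls is accumulated". The Appendix C form has numbered rows for up to five falls. The same section defines a person-level quantity separately: "A faller is defined as the participants sustained at least one fall or more".

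The test appears in three places:

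- Current synopsis (Amendment 2): "The number of falls at month 36 and adverse events will perform by chi-square test".
- Section 16.3 as replaced by Amendment 1: "The numbers of falls and adverse events will perform by chi-square test".
- The 10-year extension endpoint (Amendment 2): "Number of falls at the end of 10 years extension follow-up will be performed by chi-square test".

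The synopsis adds a time-based description of fallers, "Kaplan–Meier analysis will be calculated in order to demonstrate differences in number of fallers over time", and a Cox regression of time to first fall with a 95% confidence interval. Neither is named as the test of the primary endpoint. All tests are two-sided at 5%. No count model, follow-up offset or robust variance is given.

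**The concern.** A chi-square test needs independent units. Women are independent units here; falls are not, because one woman can contribute several. The plan names the count as the object of the test and leaves the table undefined, so there are two ways to carry it out, each with a different defect.

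- **Falls tabulated.** A few frequent fallers in one arm can create an apparent difference, because the test assumes that falls vary no more than a Poisson count.
- **Fallers tabulated.** The repeat falls that the endpoint counts are discarded, so the test answers a different question from the one posed.

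Neither version uses each woman's time at risk or gives a rate ratio with a confidence interval. This is the only confirmatory comparison, and the choice between the two versions could be made after the data are seen.

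**Working it through.** **Planning figures.** Section 11 gives 19% in the placebo group, a 50% reduction, one-sided 5%, 90% power, 55 per group, and 70 per group after 20% dropout.

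- Dropout: 55/0.8 = 68.75, so 69, which agrees with 70. Evaluable women: 70 × 0.8 = 56 per arm.
- The 55 does not reproduce from the falls inputs. Comparing 19% with 9.5% (pooled normal formula, one-sided 5%, 90% power) needs 231 per arm. Three-year cumulative risks of 1 − 0.81³ = 46.9% and 1 − 0.905³ = 25.9% need 89 per arm.
- 55 is exactly what a comparison of means gives with SD 0.89 and difference 0.5: 2 × (1.645 + 1.282)² × 0.89²/0.5² = 54.3, so 55. It may therefore have come from the lean mass and TUG calculation that Amendment 1 deleted. That is a separate point, but it means section 11 does not settle which falls measure was meant.

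**Assumptions for the error rate.** The 19% is read as 0.19 falls per woman-year, so the mean is m = 0.19 × 3 = 0.57 falls per woman. Dispersion is not in the documents; k = 0, 0.5, 1 and 2 is an assumed range (negative binomial, variance = m + k·m²). There are 70 women per arm and no treatment effect.

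**Chi-square on total falls, full follow-up.** With A and B falls in the two arms the statistic is (A − B)²/(A + B). It assumes variance/mean = 1, whereas the true ratio is 1 + k·m. The actual size is therefore about 2 × [1 − Φ(1.96/√(1 + k·m))]. The last two columns come from 40,000 simulated null trials per row.

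| k | variance/mean | size by formula | simulated, total falls | simulated, fallers yes/no |
|---|---|---|---|---|
| 0 | 1.00 | 5.0% | 5.0% | 4.8% |
| 0.5 | 1.285 | 8.4% | 8.4% | 4.8% |
| 1 | 1.57 | 11.8% | 11.8% | 4.9% |
| 2 | 2.14 | 18.0% | 17.9% | 5.1% |

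**Unequal time at risk.** Dropout times were spread evenly over the three years (assumed).

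| Dropout | total falls, k = 0 | total falls, k = 2 | fallers, k = 0 to 2 |
|---|---|---|---|
| 20% in both arms | 5.4% | 17.8% | 4.9–5.1% |
| 10% v 30% | 8.1% | 20.4% | 6.6–7.4% |

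At a slightly higher rate of 0.21 per woman-year, the fallers test reaches 7.9% under 10% v 30% dropout. A rate test with person-time and robust variance stayed at 4.8–5.2% in every scenario.

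**Power of a rate comparison.** For a rate ratio of 0.5, the means are 0.57 and 0.285. The standard error of the log rate ratio is √[(1/0.57 + 1/0.285 + 2k)/56], and two-sided power is Φ(0.693/SE − 1.96).

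- k = 0: SE = √(5.263/56) = 0.307, power 62%.
- k = 0.5: SE = 0.334, power 55% (0.545).
- k = 1: SE = 0.360, power 49%.
- k = 2: SE = √(9.263/56) = 0.407, power 40%.

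**The case against.** The strongest reply is that the chi-square was always meant for women. The same sentence applies it to adverse events. Section 12.3 defines a faller and a cumulative incidence of fallers. Section 11 plans on an incidence of 19%, and the summary of amendments says the primary analysis was aligned with the sample size. On that reading the error stays near 5% with equal follow-up. This stands as far as it goes: a reader might infer that the 5% level is certain to be lost, and the documents do not support that. But they do not settle the unit either. The synopsis gives the chi-square to falls and, in the next sentence, Kaplan–Meier to fallers. If women are tabulated, the test and the endpoint no longer match.

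Four further limits stand:

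- The dispersion values are assumed. The section 6.2 exclusions (gait, balance, strength, postural hypotension, four or more prescription drugs) plausibly make the women more alike, so k = 2 is the upper end of a range, not an expectation.
- A reader might set falls against women minus falls in a two-by-two table and obtain far larger error rates. The plan describes no such table, so no figure here rests on it.
- A reader might infer that the 20% planned dropout alone breaks the test. It does not: equal dropout changes little, and a difference between arms is needed.
- Kaplan–Meier and Cox use follow-up time and are unaffected by repeat falls. They soften the problem but do not remove it, because they stop at the first fall and are not the named primary test.

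**Conclusion.** The point holds in conditional form. The primary endpoint is a count of repeatable events, and its stated test has an undefined unit and no allowance for time at risk. Tabulating falls gives a true error of about 8%, 12% and 18% at assumed k = 0.5, 1 and 2, and about 5% only if falls are Poisson. Tabulating fallers keeps about 5% with equal follow-up but does not test the stated endpoint. With follow-up as unequal as 10% v 30% dropout, the error is about 8–20% for total falls and 6–8% for fallers. These figures rest on 0.19 falls per woman-year (0.21 for the top of the fallers range), 70 women per arm and the assumed dispersion. The mismatch between endpoint and test needs none of these assumptions. The 10-year falls endpoint carries the same undefined test; no error rate was calculated for it. Because this is the sole primary test, it should be settled before unblinding.

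**What to change.** **Preferred.** In the synopsis and section 16.3, make the primary analysis a negative binomial regression (or Poisson with robust variance) of each woman's number of falls to month 36, with log follow-up time as offset. Adjust for site and baseline fall history, which section 7.4 already collects ("Medical and medication history(including history of falls"). Report the rate ratio with a 95% confidence interval at two-sided 5%. Keep the chi-square for the proportion of fallers and the Cox model as supportive analyses. Use the same count model for falls over the 10-year extension.

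**Alternative.** Redefine the primary endpoint as the proportion of fallers or the time to first fall, so that the endpoint, the test and the 19% planning incidence agree.

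**Cost.** Mostly wording and a standard model; no new data are needed. The negative binomial model estimates one extra parameter, the dispersion. The real cost is disclosure: the power of the rate comparison must be restated, at about 62% (k = 0) to 40% (k = 2) with 56 evaluable women per arm and a rate ratio of 0.5. Reaching 90% would need 116, 137, 159 or 203 women per arm at k = 0, 0.5, 1 or 2. The shortfall comes mainly from the sample size, not from the model.

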### Section: 3.3 Rational

Add:

**After the trial, the recruited participants will be followed up in the 3rd, 6th and 10th year to assess the latent efficacy of BSYJF interventions on number of falls in late postmenopausal women. The serum 25(OH)D levels will be also measured at those three time-points.**

### Section: 5.1 Study Design

Replace:

The study duration is from January 2000 to December 2004. Subjects will be randomly assigned to receive BSYJF (n=70) or placebo (n=70) with a 1:1 allocation ratio. The study will carry out at the two sites (Institute of Orthopaedics and Traumatology, Shanghai Academy of TCM; and Shuguang Hospital). A total of 140 participants will be selected from two sites to participate in the study.

With:

**The study will be carried out from January 2000 to December 2014, comprised of a 36 month treatment phase and followed by a 10-year extension phase without treatment.** Subjects will be randomly assigned to receive BSYJF (n=70) or placebo (n=70) with a 1:1 allocation ratio. The study will carry out at the two sites (Institute of Orthopaedics and Traumatology, Shanghai Academy of TCM; and Shuguang Hospital). **At the beginning of the study, a total of 140 participants will be selected from two sites to participate in the study.**

### Section: 6.2. Exclusion Criteria

Add:

**For the extension phase, additional exclusion criteria have been defined to protect subjects who have experienced a large bone loss or fragility fracture during the initial 36 month treatment phase of the study.**

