**Rationale:**

In the vast majority of cases, a hip fracture is a fragility fracture due to a fall or minor trauma in someone with osteoporotic bone. Risk factors of hip fractures observed are expected to be of long duration. However, BSYJF treatment was designed initially 36 months. Instead, a 10 year extension phase is added to explore the effect of transitioning from 36 months of treatment. The main objective of this extension phase is to evaluate if latent effects of BSYJF that might be lower fall rate and even hip fracture rate. In other words, 10 years extension follow-up of treatment cessation can be studied and is an accepted clinical approach.

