**Introducing a 10 years extension follow-up phase:**

Active intervention will take place over 3 years until the end of 2004. After the trial, the recruited participants will be followed up in the 3rd, 6th, and 10th year to assess the latent effects of BSYJF interventions on fall and hip fracture incidence rate in late postmenopausal women.

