|-----------------------------------|----------------------------------------------------------------------------------------------------------------------------------------------------------------------------------------------------------------------------------------------------------------------------------------------------------------------------------------------------------------------------------------------------------------------------------------------------------------------------------------------------------------------------------------------------------------------------------------------------------------------------------------------------------------------------------------------------------------------------------------------------------------------------------------------------------------------------------------------------------------------------------------------------------------------------------------------------------------------------|
|                                   | 
1.5 mg/dl.
 
Additional exclusion criteria have been defined to protect subjects who have experienced a large bone loss or fragility fracture during the initial 36 month treatment phase of the study.
                                                                                                                                                                                                                                                                                                                                                                                                                                                                                                                                                                                                                                                                                                                                                 |

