**Additional endpoint:**

**Number of falls at the end of 10 years extension follow-up will be performed by chi-square test.**

Section: 17.2 Diet and Exercise Control

Add:

During the entire trial, the subjects will be advised to follow the guideline for daily dietary intake and physical activities, such as intaking high-protein diet, avoiding alcohol abuse and smoking, and keeping active in daily physical activities. The questionnaire for daily dietary intake and physical activities should be recorded at 12, 24, 36 months during 36-month clinical trial **and at the 3rd, 6th and 10th year during 10-year follow-up.** Calcium and vitamin D supplement on their own should be prohibited in 36-month clinical trial.

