### **Rationale and Changes (Original Protocol 1.1 to Version 1.2):**

To assess the latent effects of BSYJF interventions on number of falls in late postmenopausal women, eligible subjects will enter a 10 year extension phase at the end of the initial 36 months treatment phase. Some changes were updated to be aligned with the trial.

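### Entry to the untreated 10-year extension depends on bone loss and fracture during treatment, so the latent-effect comparison of falls is open to selection bias of unknown size and direction

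*Supplement*

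**What the plan says.** Amendment 2 (version 1.2) is the latest version. Its Section 5.1 describes 36 months of treatment "followed by a 10-year extension phase without treatment". The stated aim is "to assess the latent effects of BSYJF interventions on fall and hip fracture incidence rate" in late postmenopausal women, and the rationale speaks of seeking to "evaluate if latent effects of BSYJF that might be lower fall rate and even hip fracture rate".

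The entry rule appears in two places. Section 6.2, under exclusion criteria, says that for the extension "additional exclusion criteria have been defined to protect subjects who have experienced a large bone loss or fragility fracture during the initial 36 month" period. The synopsis repeats it: "Additional exclusion criteria have been defined to protect subjects who have experienced a large bone loss or fragility fracture". Neither place lists the criteria or gives a threshold for large bone loss. The summary of amendments says that "eligible subjects will enter a 10 year extension phase at the end of the initial 36 months treatment phase", and the addition to Section 9 asks the women who are included to record their falls. The analysis is one line: "Number of falls at the end of 10 years extension follow-up will be performed by chi-square test".

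Other passages point the other way. The statistical considerations in the same synopsis state: "All the analyses will use all randomly assigned patients under ITT principle". The introduction of the extension and the addition to Section 3.3 both say that the women recruited to the trial will be followed up in years 3, 6 and 10, and neither mentions an eligibility step.

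**The concern.** Large bone loss and fragility fracture during treatment are results of the trial. Month-36 change in femoral neck BMD is a secondary endpoint, and the Amendment 2 rationale itself describes hip fracture as arising from a fall or minor trauma in osteoporotic bone. If BSYJF acts on bone as hypothesised, different fractions of the two arms, and different kinds of women, would be filtered out before the extension starts. The women left are then not the groups that randomisation formed, and the planned chi-square test makes no adjustment.

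At stake is the 10-year answer on latent effect. If excluded women supply no extension falls, no later analysis can restore them. Applying LOCF to them would only carry forward their 36-month count.

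**Working it through.** The plan gives no sample size, power or exclusion rate for the extension, so there is no stated figure to reproduce. The check is first one of text, then an illustration of size.

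**1. The passages side by side.** Section 6.2, the synopsis eligibility row, the addition to Section 9 and the summary of amendments limit the extension to women who pass criteria judged on months 0–36. The ITT sentence in the synopsis, the introduction of the extension and the addition to Section 3.3 refer to all women randomised or recruited. Nothing provides for following excluded women, adjusting for the selection, or reporting exclusions by arm. An ITT label does not settle the conflict, because women who are not observed contribute no extension falls.

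**2. When bias arises.** Two conditions must both hold: treatment affects who is excluded, and the excluding outcome is related to later falling. If either fails, the comparison stays balanced.

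**3. Illustration on the rate scale, no true latent effect.** All inputs are assumptions: exclusion of 20–30% of placebo and 10–15% of BSYJF women; correlation ρ of 0.2–0.4 between bone/fracture score S and fall-proneness Z (both standard normal); gamma-distributed individual fall rates with mean 1 and CV 0.7–1.0. Women with S above c(q) = Φ⁻¹(1 − q) are excluded. With G the gamma distribution function (shape 1/CV²), the mean rate among those kept is

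m(q) = ∫ G⁻¹(Φ(z)) φ(z) Φ((c(q) − ρz)/√(1 − ρ²)) dz / (1 − q),

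and the apparent rate ratio is m(q BSYJF)/m(q placebo).

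| ρ | CV | Excluded, placebo / BSYJF | m placebo | m BSYJF | Ratio |
|---|---|---|---|---|---|
| 0.2 | 0.7 | 20% / 15% | 0.952 | 0.962 | 1.01 |
| 0.2 | 0.7 | 20% / 10% | 0.952 | 0.973 | 1.02 |
| 0.4 | 1.0 | 20% / 10% | 0.860 | 0.917 | 1.07 |
| 0.4 | 1.0 | 30% / 15% | 0.809 | 0.887 | 1.10 |
| 0.4 | 1.0 | 30% / 10% | 0.809 | 0.917 | 1.13 |

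The first and last rows are the extremes of the grid. Simulation with 2,000,000 women per arm puts the top at 1.136, so the range is about 1.01 to 1.14. At ρ = 0.1 the ratio is about 1.005 to 1.03, and at ρ = 0 it is 1.00. With equal exclusion and the same selection in both arms it is also 1.00. If the exclusion rates are swapped between arms the ratios invert: 1/1.01 = 0.99 to 1/1.14 = 0.88.

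**4. Loss of sample.** With 1:1 allocation the overall loss is (20 + 10)/2 = 15% to (30 + 15)/2 = 22.5%, or 21 to about 32 of 140 women, before any other loss.

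**5. Size against sampling noise.** A second model, on the risk scale, lets a frailty U ~ N(0,1) drive both exclusion and later falling (logit of fall risk = 0.8 + U), again with no true effect.

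- Exclusion 22% in both arms: difference among retained women 0.0 points.
- Exclusion 22% placebo, 11% BSYJF: retained fall risk 62.6% and 64.2%, a false difference of 1.6 points. About 55 and 63 of 70 remain. SE = √(0.626·0.374/55 + 0.642·0.358/63) = 8.9 points, so the bias is 1.6/8.9 ≈ 0.2 SE.
- Exclusion 42% and 22%, with stronger dependence on frailty: 56.2% and 61.0%, a false difference of 4.8 points. About 40 and 54 remain. SE = √(0.562·0.438/40 + 0.610·0.390/54) = 10.3 points, so the bias is about 0.5 SE.

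**The case against.** The criteria are described but never listed, so how many women they would remove is unknown, and every input above is assumed. Sections 3.1 and 3.3 separate bone-dependent risk factors from the bone-independent ones (muscle and mobility) and link falling mainly to the latter. For the bone-loss criterion, a correlation with falling near zero is therefore plausible, and the bias would then be negligible. In the illustrated cases it is well under one standard error. Only an additional endpoint is touched. All of this stands, and it limits the weight of the point.

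It does not remove the point. Fragility fracture is tied to falling by the amendment's own rationale, and exclusion is the plain reading of text placed under exclusion criteria and backed by an eligibility gate.

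A reader might infer three stronger things that the documents do not support:

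- **That the 10-year result is uninterpretable.** The illustrated distortion is modest, and it vanishes under either condition in step 2.
- **That the bias must run against BSYJF.** That follows only if BSYJF lowers exclusion and the excluded women fall more. The documents fix neither.
- **That the exclusion protects nobody.** The extension gives no trial treatment, and the updated Table 1 schedules only falls and the diet and activity questionnaire (Section 3.3 adds serum 25(OH)D), so no protective purpose is evident for ending observation. But the rule is unseen, and its clinical reasoning cannot be judged from here.

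**Conclusion.** The point holds as a risk. The extension's between-arm comparison of falls is made in women selected on post-randomisation outcomes that treatment is expected to affect, so it is open to selection bias whose size and direction cannot be determined from the plan. The entry rule also contradicts the plan's own ITT and follow-up wording. If exclusions fall mainly on placebo, a spurious rate ratio of about 1.01 to 1.14 is a reasonable illustration. This rests on assumed exclusion rates, correlation and heterogeneity, and it is 1.00 when bone status is unrelated to falls or treatment does not affect exclusion. The 36-month primary endpoint and the month-36 secondary endpoints are unaffected. This should be fixed, but it does not threaten the main result.

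**What to change.** Reconcile the extension entry wording (synopsis eligibility row, Section 6.2, addition to Section 9, summary of amendments) with the ITT sentence in the synopsis, the introduction of the extension and the addition to Section 3.3, so that meeting an extension criterion does not end outcome observation. Specifically:

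- List the criteria and state what they govern. Any protective clinical care for these women is for the sponsor to decide.
- Record falls at years 3, 6 and 10 for every randomised woman who consents, whatever her bone or fracture status at month 36. Record fractures at the same contacts: the Appendix C form already has the boxes, and the stated aim names hip fracture.
- Extend the Table 1 row for concomitant disease and medication to those contacts and add vital status, so that care given outside the trial is data and not a reason for removal.
- Compare the arms as randomised, and report by arm how many women met the extension criteria.

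The cost is an amendment to the wording, contact with a modest number of additional women at three time-points (about 21 to 32 under the illustrated rates), and a few more entries per contact. The excluded women have no extension visits scheduled at present, so those contacts are a real addition.
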